## 1. Introduction

### 1.1. Background and Rationale

Family Skills Training offers a combination of parenting knowledge, skill building, competency enhancement, and support [1]. Family skills packages have been designed to reduce current family relationship problems and prevent future difficulties through training, support, or education [2]. They aim to strengthen family protective factors, such as communication, trust, problem-solving skills, and conflict resolution, and often include opportunities for parents and children to spend positive time together as a way to strengthen the bonding and attachment between the two.

Family skills training programmes have frequently been used at a universal level of prevention. As such, they target whole populations, most frequently through schools, neighbourhoods, or communities, without specific screening at the individual level for the level of risk presented. Such universal approaches share the assumption that almost anyone can benefit from such a prevention and health promotion/orientation package, and that delivery to groups made up of families with differing levels of risk is likely to foster engagement. Such an approach also has the potential of reducing any potential stigmatization of the programme, in the sense of associating it with targeting families with specific problems and facilitating as many families as possible to benefit from it. Nevertheless, such a universal approach does not necessarily mean that the package affects all families equivalently; but, the aim is always to mostly benefit those families facing higher levels of challenges. Individual cases with higher levels of problems will be identified by facilitators and referred to more tailored or individualised services [3].

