#### 2.11.3. Quantitative Statistical Methods and Qualitative Data Analysis

A mixed method approach using quantitative and qualitative measures will be used. Quantitative measurements will evaluate potential effectiveness, including a prospective collection of outcome data assessing changes in children’s behaviour, parenting skills, and family adjustment in caregivers. In addition, qualitative interviews will facilitate an understanding of the caregiver’s experience in taking part in the intervention and the cultural acceptability.

We will follow CONSORT guidelines for reporting and quantitative analysis. Statistical analysis will be undertaken by a researcher with relevant expertise and an analysis of quantitative measures will be conducted upon completion of the final measures, three months post-intervention.

All data will be analysed according to the intention to treat. Ideally, all participants will be followed up with, as has previously been performed. In case of a loss of follow-up or not all questions being answered, a non-responder analysis will be performed and those who did not attend a follow-up will be compared to the remaining. Missing data will be excluded from the analyses or imputed using the serial mean, depending on the amount of missing data.

The normality of the data distribution will be assured through a visual inspection of the histograms, Q-Q plots, and box plots. Cronbach’s alpha coefficients will be calculated to assess internal consistency.

For demographic data, continuous variables will be presented as means and standard deviations (SD), with a 2-sample *t*-test for comparison; whereas, categorical data will be summarised as frequencies and proportions and compared using a chi-square test. In case of non-normality, the respective non-parametrical tests will be used.

To compare scores at the different time points, we will conduct a two-way multi-level mixed ANOVA (time: within-subjects factor and group: between-groups factor), considering the subject and the territory random effects. This overall analysis will be followed by the simple effect analysis, if the interaction is significant, and by post hoc tests for the main effect of time, if significant, using use a method based on the false discovery rate (e.g., Holm’s correction), proportional to the size of the difference between the means.

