Regression analyses (SEM) will also be conducted between the parental dimensions and the filial dimensions to evaluate the effect of parental change on the behaviour and emotional state of the child.

Stratified analyses will be conducted by gender, as well as for participants with worse scores (below the 33rd or above the 66th percentile) at baseline. Statistical significance will be set at a *p*-value lower than 0.05.

Qualitative data will be analysed using thematic analysis (TA) [31], where dominant themes will be identified through a close examination of the data. First, open coding will be carried out and an initial coding schedule will be devised in order to define each emerging theme. The coding manual will then be revised throughout the coding of the remaining transcripts. The original codes will frequently be combined or divided into further codes, depending on the emergent findings. Themes will be continually compared with newly coded interview transcripts to ensure that they are readily applicable to the data by using the research team’s familiarity with the text and coding manual to frequently assess and reassess how the codes are being applied to the raw data. The coding manual will be discussed within the research team and amendments will be made if necessary. The team will then develop a revised code set that includes the new and combined codes. NVivo9 software will be used to facilitate the analysis. The analysis will cease when the research team judges that thematic saturation has been reached [31].

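### Separate stratified analyses by gender and in the worst baseline third cannot show whether the programme effect differs, and the tests run inside the strata are not stated

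*Protocol article*

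**What the plan says.** All the relevant analysis text is in section 2.11.3 of the protocol article.

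- **Main analysis:** a "two-way multi-level mixed ANOVA (time: within-subjects factor and group: between-groups factor), considering the subject and the territory random effects".
- **Follow-up steps:** "This overall analysis will be followed by the simple effect analysis, if the interaction is significant", and then "by post hoc tests for the main effect of time, if significant". Both steps are attached to the overall analysis. The second depends on a significant time effect, not on a difference between the arms.
- **Strata:** stratified analyses are planned by gender and for "participants with worse scores (below the 33rd or above the 66th percentile) at baseline". The significance threshold, in the next sentence, is a p-value "lower than 0.05".

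The section names no model for the strata and no test that the effect differs between them. It names no counterpart to the worst-scoring third, and it does not say whether gender means the child's or the caregiver's; section 2.10 collects both.

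Section 1.1, on universal family skills approaches in general, says that "the aim is always to mostly benefit those families facing higher levels of challenges". The objectives in section 1.4 do not repeat this as a hypothesis of the trial.

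**The concern.** A subgroup analysis is useful if it shows whether the programme works differently for boys and girls, or for families who start in more difficulty. Analysing each stratum separately at 0.05 does not answer that. A significant result in one gender and a non-significant one in the other is a common chance outcome when the effects are equal, and it is easily reported as a gender difference. For baseline severity there is not even a pair to compare. A result in the worst third, significant or not, says nothing about whether those families gain more or less than the rest.

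The second risk depends on something the article leaves open. If the overall procedure is repeated inside the worst third, it includes a test of change over time. A group selected for bad scores is expected to look better at the next measurement in both arms, with or without the programme. A significant time effect there could then be described as improvement in the families with the greatest need.

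**Working it through.** **1. The plan's own figure.** Table 4 gives 40 for PAFAS parental adjustment at 80% power and 54 at 90%. The paired formula n = ((z₀.₉₇₅ + z_power) × SD_diff / mean_diff)² gives:
- 80%: ((1.960 + 0.842) × 2.7 / 1.2)² = 39.7, so 40
- 90%: ((1.960 + 1.282) × 2.7 / 1.2)² = 53.2, so 54

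Both reproduce. They are sample sizes for a before-after change in one group. The article gives no figure for the strata.

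**2. Stratum sizes.** I read 160 families as 40 × 2 arms × 2 sites, so 80 per arm. An even gender split (assumed) gives 40 per arm in each gender. The worst third of 160 is about 53 families.

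**3. Gender strata.** Assume the same true effect of 0.4 SD in both genders, a two-sided test and no clustering.
- Noncentrality = 0.4 × √(40/2) = 1.79, so power per stratum is about 42%.
- P(exactly one gender significant) = 2 × 0.42 × 0.58 = 0.49.
- With 0.44 SD (1.2/2.7, parental adjustment in Table 4) instead, power per stratum is 51% and the probability is 50%. With 40 per arm in total, power is 29% and the probability 41%.

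**4. Regression to the mean in the worst third, SDQ total difficulties.** Table 4 gives SD before 5.0, SD after 4.4 and SD of change 3.7.
- Implied correlation: r = (5.0² + 4.4² − 3.7²) / (2 × 5.0 × 4.4) = 30.67 / 44 = 0.70.
- The mean of the worst third of a normal distribution lies 1.091 SD from the overall mean.
- Expected fall with no programme effect and a stable SD: (1 − 0.70) × 1.091 × 5.0 = 1.64 points. It is 1.1 at r = 0.8 and 2.2 at r = 0.6.
- The baseline variance within the worst third is about 0.28 of the full variance. The SD of change there is √(0.30² × 0.28 × 25 + (1 − 0.70²) × 25) = 3.66.
- Paired t-test on 53 families: 1.64 / 3.66 × √53 = 3.26, giving p < 0.05 with probability about 89% (73% at r = 0.8, 96% at r = 0.6).

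**5. The same question with the planned type of test.** Null trials were simulated with no change in either arm, three time points and equal correlations. The worst third was taken from both arms pooled. Mixed-ANOVA F tests were used, with 2,000 runs and no clustering. The percentages are significant results at 80 per arm:

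| r | Main effect of time | Group × time | Before-after t-test, intervention arm only |
|---|---|---|---|
| 0.6 | 98% | 5% | 71% |
| 0.7 | 91% | 5% | 62% |
| 0.8 | 74% | 5% | 42% |
| 0.9 | 44% | 5% | 24% |

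With 40 per arm and r = 0.7, the time effect is significant in 64% and group × time in 5%. The artefact is confined to the time and within-arm tests.

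**6. What a proper interaction test would offer.** For a gender difference in effect as large as 0.44 SD, the standard error is √(4/40) = 0.316 SD at 80 per arm. The ratio is 0.444 / 0.316 = 1.41 and power is 29%. At 40 per arm the standard error is √(4/20) = 0.447 and power is 17%.

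**The case against.** The strongest reply is that the time tests are not stated for the strata. That is correct. A reader might infer that the strata keep the main-effect-of-time tests, but section 2.11.3 attaches those steps to the overall analysis and names no stratum model. The artefact in steps 4 and 5 is therefore conditional.

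A reader might also infer that regression to the mean will produce a false programme benefit in the worst third. The documents do not support that. Both arms are selected by the same rule and the waitlist arm is measured at every time point, so group × time keeps its 5% level. Simple effects are reached only after a significant interaction, and nothing says a time effect will be read as benefit. Nor does regression to the mean apply to the gender strata, where the issue is low power and chance.

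It is tempting to say that the trial claims greater benefit for higher-need families and fails to test it. The sentence in section 1.1 is background on universal programmes, not a hypothesis.

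Finally, interaction terms and an exploratory label are often left to an analysis plan, which is not shown. That would answer a complaint about missing detail. It does not answer the choice the article does make, which is separate stratified analyses with only the worst third on the severity side. That method cannot show a difference in effect.

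The inputs are also soft. The correlation comes from 14 pilot respondents measured before and after the programme, and the 0.4 SD effect and even gender split are assumptions.

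**Conclusion.** The point holds in two parts of different strength.

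The firm part is that separate stratum tests at 0.05 do not assess whether the effect differs by gender or baseline severity. With equal true effects of 0.4 SD, about half of trials (49%) would show significance in exactly one gender, and the severity analysis has nothing to be compared with. This rests on 80 families per arm, an even split, no attrition and no clustering; clustering would generally lower power further.

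The conditional part is that the tests inside the strata are unspecified. If the overall procedure is repeated in the worst third, a time effect is expected in about 90% of trials with no programme effect at r = 0.70, or 74–98% for r between 0.8 and 0.6. The randomised contrast is not affected.

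These are secondary analyses and the main comparison is untouched. The change should be made before the data are analysed.

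**What to change.** In section 2.11.3, replace the stratified tests with moderation terms in the full-sample model: group × time × baseline score, preferably continuous, and group × time × gender, stating whether this is the child's or the caregiver's. Report the between-arm difference with its 95% confidence interval for each gender and at low, middle and high baseline scores. State that any subgroup benefit will be judged on the between-arm contrast, not on time or within-arm tests. Label the results exploratory.

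The cost is a few sentences and model terms, with no new data. The downside is the imprecision in step 6, which should be reported openly: a non-significant interaction would not show that the effects are equal.

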#### 2.11.4. Data Monitoring, Quality Assurance and Potential Harms

The data monitoring committee (DMC) will consist of the project managers in each of the sites in Italy, as well as the research assistants on site. In addition, three programme (support) and evaluation managers at UNODC headquarters (HQ) will contribute. The DMC will continuously report to the programme manager and the Chief of the Section at the UNODC. The DMC is independent from any sponsors and all members declare that they have no competing interests.

We do not plan to perform any thorough interim analyses; however, data completeness and quality controls will be performed as soon as the baseline measurements are completed for both groups. We do not foresee the necessity to terminate the trial before the anticipated date as no harm, adverse events, and other unintended effects of the intervention or trial conduct are to be expected.

#### 2.11.5. Auditing

As this is a fairly brief intervention and trial, we have not planned to conduct any auditing trials and, hence, have not defined the frequency and procedures.

### 2.12. Ethics and Dissemination

#### 2.12.1. Research Ethics Approval

All procedures performed in studies involving human participants were in accordance with the ethical standards of the institutional and/or national research committee and with the 1964 Helsinki Declaration and its later amendments or comparable ethical standards. This study has undergone an internal review performed within UNODC HQ. We designed and conducted our study based on the ethical standards developed by UNICEF and have taken all procedures into account. According to these standards, the submission of a trial such as ours is not mandatory for submission to a National Ethics Review Board or Institutional Review Board; however, this study should be reviewed by at least 3 experts. In our case, we collaborated with a number of stakeholders, apart from the experts from the UNODC, including the University of Parma and the University of Parma, where at least 3 independent researchers had reviewed this study thoroughly. Nevertheless, the protocol of this study, including all tools was submitted to the Research Ethics Board University of Parma, Protocol number 0238338; and received approval.

#### 2.12.2. Protocol Amendments

We do not plan to make any amendments to the protocol, such as changes to eligibility criteria, outcomes, or analyses. If it would, however, be necessary to change any of these, we would communicate any change immediately to all relevant parties, such as all investigators in the field, as well as HQ, REC/IRBs, trial participants, trial registries, and journals.

#### 2.12.3. Consent or Assent

Consent will be obtained through caregivers completing a consent form at the beginning of their appointment to complete the questionnaires at the first evaluation meeting. In addition to written information being provided in the form of the participant information sheets for the parents, participants will be provided with a verbal explanation of the evaluation method at the first meeting and again when they attend the first data collection session. If participants are only able to give verbal consent or assent, this will be audio-recorded.

Children and youth will complete assent forms, complementing the consent forms of their caregivers, in case they are under the age of 18 years as this is the legal age in Italy.

#### 2.12.4. Confidentiality

The chief investigator and the research team will preserve the confidentiality of participants in accordance with the Data Protection Act of 1998. All questionnaire data from participants will be either collected through Google Forms or conventionally on paper, with the process evaluated using digital recorders for the interviews. Identifying material will be removed as soon as possible from transcripts and notes. Each participant will be assigned a unique identification number and this will be used on all paper questionnaires and databases into which the data will be entered. Electronic copies of transcripts will be held separately from digital recordings of interviews and the file containing the participants’ names and corresponding numbers. All data collected as part of the trial will be treated as confidential and will only be viewed by members of the trial team; anonymised data will be used wherever possible.

Facilitators will be assigned a number that will be used on all reflection sheets and evaluations. Facilitator numbers will be stored using a password-protected file. The project manager and senior research team will be the only members of the research team holding a record of the individuals’ names corresponding to the facilitators’ numbers.

#### 2.12.6. Access to Data

After data cleaning and analysis, the anonymised datasets will be made available in a publicly available open database (i.e., Mendeley Data repository, OpenTrials, EudraCT, ICPSR, etc.).

#### 2.12.7. Ancillary and Post-Trial Care

Families in the control group (=waitlist group) will receive the intervention after the completion of all data collection points. Post-trial care will be service-as-usual. We do not expect anyone to suffer harm from the intervention; but, in the past, we have heard feedback from families who wish to have additional sessions of the programme, even after completion. We are currently working on add-on modules for the programme and hope to be able to offer these to families through the facilitators. In addition, a mobile phone application for families is currently being developed; however, roll-out is unlikely before the start of this trial.

#### 2.12.8. Dissemination Policy

Findings will be disseminated nationally to investigators, facilitators, and interested families straight after the completion of the analysis. Internationally, results will be disseminated to policymakers through presentations, in peer-reviewed journals to fellow researchers, through the UNODC website to the public, and through reports to donors.

Standard authorship eligibility criteria will be applied; we do not intend to use professional writers for upcoming publications of results but rather compose an author team based on the investigators/researchers involved in the trial. Through publication of this manuscript, we already grant public access to the full protocol and, if requested, we can share the anonymised participant-level dataset, once available, as well as the statistical codes.

## 3. Summary

Italy, particularly given the implication of two universities in this process, represents an ideal location for trialling Family UNited, given the existence of strong examples of the promotion of prevention based on science. Italy has been a country engaged with the UNODC on the development and dissemination of the UNODC WHO International Standards on Drug Use Prevention and has several health authorities and university centres that have been implicated in EU (European Union)-centred prevention initiatives, including the European Drug Addiction Prevention Trial that developed UNPLUGGED [32], the European Drug Prevention Quality Standards (EDPQS) Toolkits [33], the European Prevention Curriculum (EUPC) [34], and related training materials. Such a model of implementation would be significant to further supporting European Union efforts by introducing a tool with high scalability potential, supporting the EU Drug Strategy 2021–2025.

While Family UNited was initially developed in line with the UNODC WHO International Standards on Drug Use Prevention, making it primarily a drug-prevention programme, the etiological model addressed by these standards addresses a vulnerability that is common to many other social and health outcomes beyond drug use. Such outcomes include violence, mental health, and other risky behaviours. Given the easier proximity (timewise) to assess indicators of violence and mental health, these would be given priority. By measuring attitudes to violent behaviour and parental skills, we intend to measure changes on this domain, potentially leading to improvements on the targets set for the Sustainable Development Goal (SDG) indicators 16.1.3 (prevalence of all forms of violence).

Even though this trial is in a high-income country, such results complement the existing experience of the feasibility and efficacy of Family UNited previously piloted in LMIC, with impact-related measures encouraging the adoption of such approaches globally and beyond the EU borders. We would hope this trial will offer the opportunity to further strengthen the positive change of the culture of prevention by adding an open source and readily scalable tool to the registries of evidence in order to support more and more families globally and, more valuably, further support member states in reaching their sustainable development goals on the road to 2030.

## 4. Trial Status

After submitting this protocol for peer-reviewed publication, we received approval from the ethics committee review started the trial already. 

## 5. Standards of Reporting

This manuscript was prepared based on the “SPIRIT 2013 Statement” for reporting protocols of clinical trials [35].

## 6. Protocol Version

Version 1; 17 November 2022.

## Figures and Tables

**Figure 1 ijerph-20-06548-f001:**
[figure not shown]
Family UNited logic model [19].

**Figure 2 ijerph-20-06548-f002:**
[figure not shown]
Family UNited RCT schema.

**Figure 3 ijerph-20-06548-f003:**
[figure not shown]
Data collection scheme.

**Table 1 ijerph-20-06548-t001:** Family UNited structure [19].

	Caregiver Session	Child Session	Family Session
**Week 1**	Understanding praising and encouraging children	Building positive qualities	Our family’s positive qualities
**Week 2**	Changing challenging behaviour	Handling stress	Learning about each other
**Week 3**	Responding to un-desirable behaviour	Skills to resist peer pressure I	Understanding peer pressure and family connections I
**Week 4**	Communicating and taking care of yourself	Skills to resist peer pressure II	Understanding peer pressure and family connections II

**Table 2 ijerph-20-06548-t002:** Dummy table of process evaluation components, data sources, and indicators.

Process Evaluation Component	Data Source	Indicator	Caregiver				Child				Family				Total
			Session 1	Session 2	Session 3	Session 4	Session 1	Session 2	Session 3	Session 4	Session 1	Session 2	Session 3	Session 4	
Dose delivered	Coordinator	Number of sessions delivered													
Fidelity	Observer	Percentage of activities reported as covered													
	Facilitator	Percentage of activities reported as fully/mostly covered as 3/4 (on a scale of 1 [not/hardly] to 4 [fully])													
	Observer	Percentage of programmes with ≥2 facilitators at every session													
	Observer	Percentage of programmes with ≥1 of the same facilitators at every session													
	Observer	Percentage of programmes with >4 and <15 families													
Dose received	Facilitator	Percentage of activities reporting interest of young people; and parents/carers as 3/4 (on a scale of 1 [low] to 4 [high])													
Reach	Observer	Percentage of families attending all 4 sessions													
Inputs	Observer	Percentage of sheets with a good or very good evaluation of the quality of childcare and travel arrangements													
	Observer	Percentage of sheets with a positive evaluation of (area of) refreshments													
	Observer	Percentage of sheets with a positive evaluation of room/materials/equipment													

**Table 3 ijerph-20-06548-t003:** Timeline of the pilot study and RCT.

Week	Activity
	PILOT STUDY
Week 1	Recruitment of 2 Research Assistants and training on measure completion
Week 2	Research Assistants recruit 10 families.
Week 2	Research Assistants conduct baseline measures and consent (Time 1) with all 10 families
Week 3–6	Families take part in weekly sessions of Family UNited for 4 weeks
Week 6	All families’ complete measures again (Time 2)
	RCT
Week 1–2	Research Assistants assess families for eligibility and inform them about the planned trial and the programme verbally and in writing
Week 3	Research Assistants recruit 160 families, obtain written assent/consent and conduct baseline measures (Time 1; pre-intervention) with all families After data collection has been completed, families are randomly allocated to intervention or control group
Week 4–7	Intervention group families take part in weekly sessions of Family UNited for 4 weeks Facilitators and observers complete process evaluation tools after each session
Week 9	ALL families complete measures again (Time 2; post-intervention). 10 caregivers from the intervention group are interviewed for acceptability
Week 13	ALL families complete measures again (Time 3; follow-up)
Week 14–17	Control families take part in weekly sessions of Family UNited for 4 weeks

**Table 4 ijerph-20-06548-t004:** Sample size estimates based on selected (statistically significant in paired *t*-test *) results from the pilot trial for Family UNited in Parma and Trentino, Italy, in spring 2022 [25].

	Before: Mean ± SD	After: Mean ± SD	Paired Difference in Means ± SD	Sample Size (Power)	
PAFAS				80%	90%
Positive encouragement (*n* = 14)	5.1 ± 2.3	2,1 ± 1.2	3.0 * ± 2.7	**10**	**12**
Parental adjustment (*n* = 14)	5.9 ± 3.1	4.7 ± 2.7	1.2 ± 2.7	**40**	**54**
Family relationships (*n* = 14)	3.8 ± 2.3	2.9 ± 1.7	0.9 * ± 1.2	**17**	**21**
SDQ					
Hyperactivity (*n* = 14)	2.8 ± 2.1	2.1 ± 1.8	0.7 * ± 1.1	**23**	**30**
Conduct problems (*n* = 14)	2.6 ± 1.8	1.3 ± 1.1	1.4 * ± 1.4	**12**	**15**
Total Difficulty Scale (*n* = 14)	10.9 ± 5.0	8.4 ± 4.4	2.6 * ± 3.7	**20**	**26**
CYRM-R					
Total CYRM (*n* = 12)	58.8 ± 19.0	60.8 ± 18.2	1.9 ± 6.9	**104**	**138**
Personal resilience (*n* = 12)	35.8 ± 11.8	37.4 ± 11.3	1.7 ± 3.9	**45**	**61**

